#### Power analysis

To estimate the power to detect statistically significant effects for the relations specified in the MLM, the power program RMASS was used. This program is specifically designed to calculate power for longitudinal data with attrition when a comparison between groups (e.g., current implementation vs. TCT) is of primary interest. To estimate the power, several assumptions were made: (1) An alpha level of .05 (2) a conservative effect size of *d* = .61 (we consider this conservative because a meta-analysis [39] of teamwork interventions reported a large effect size of .92), (3) standard deviations at each time-point that were increasing in magnitude (baseline: SD = 1.00 with SDs increasing by .5 at each subsequent time-point, (4) an overall attrition rate of 15% was specified based on our current trials, and (5) a stationary autoregressive structure (lag 1) was specified for the variance–covariance matrix of the repeated measures, using an autocorrelation value of .70. Given these assumptions and with a sample of 10 clinicians from 4 clinics (*n* = 20 in each implementation arm), we will have 80% power to detect the predicted effect on outcomes.

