Aim 2 will utilize a cluster randomized design in which four specialty care clinics (10 clinicians per clinic; *n* = 40 clinicians) responsible for reviewing and responding to depression screening (youth ages 12–17 years) will be matched and then randomized to a TCT condition (two clinics) versus an early identification universal depression screening condition (two clinics). Clinics will be matched on team size, makeup of the team members, type of medical care focus and then randomized to conditions. Thus, there will be two sets of two matched clinics that will then be randomized, one to the TCT and the other to early identification universal depression screening condition. In the comparison implementation strategy (early identification universal depression screening), multiple discrete strategies will be used including depression screening training in which providers and staff are provided 1) training in the depression screening tool (PHQ), 2) orientation to the clinical pathway (i.e., screening conducted at every urgent care or emergency department visit and every 30 days for all other medical visits), and 3) expectations for handoff to the next step in the care cascade.

The TCT will last 6 months and is proposed to include the following components that will be refined based on Aim 1 findings and developmental activities: Two initial 2-h didactic sessions on effective communication between team members (information-based methods) and simulation exercises based on mock clinical cases (practice-based methods), biweekly performance feedback about intra-team communication in the EHR (demonstration-based methods) provided during regularly scheduled supervision meetings, and a 1 h booster coaching sessions approximately every 2 months over a 6-month period.

#### Specific Aim 3

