### Data management

#### Analytic plan

For Aims 2 and 3, we will use multilevel modeling with random intercepts and slopes to test the preliminary effects of TCT on implementation and service outcomes (Aim 2) and mechanisms (Aim 3). Refer to Table 2 for measures of outcomes and mechanisms. Specifically, outcomes include team member-reported acceptability, appropriateness, feasibility and workflow efficiency, and child service outcomes. Potential mechanisms are the proposed mediators of implementation climate, psychological safety climate, communication/coordination, and shared cognitions (see Table 2). Clinic will be included as a covariate (fixed effect). To test the effects of TCT a Group [current implementation vs. TCT] X Time [Baseline, 3, 6 Months] cross-level interaction will be assessed for each outcome. If a statistically significant (*p* < .05) interaction term is evident, simple slopes analyses will be conducted.

Quantitative data and qualitative data will be first analyzed separately. First, quantitative analyses of mechanisms of the TCT implementation strategy will be analyzed using the analytic approach described in Aim 2. To examine the hypothesized mediated effects of implementation strategy condition on implementation and service outcomes, multilevel path analysis will be conducted. Measures of Implementation Climate, Intra-Organizational Alignment, Communication and Coordination, Shared Cognitions, and Psych Safety will be tested as mediators in respective models. The specific mediated effects within these models will be tested using the bias-corrected bootstrap approach [38]. Qualitative interview data will be analyzed using rapid qualitative methods [28] based on a templated summary, deductive approach focused on specified team mechanisms. Specifically, the research team will code transcripts for changes in proposed mechanisms as explanatory factors in implementation and service outcomes. We will then use a mixed-methods analytic approach to synthesize the qualitative and quantitative data collected to examine convergence (i.e., do the two methods confirm or find similar results), complementarity (i.e., do the two methods provide more depth of understanding of research questions), and expansion (i.e., do the two methods provide insights beyond either method alone).

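### The stated 80% power takes no account of randomising four clinics, and the printed inputs reach it only under an effect shape the article does not state

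*Protocol article*

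**What the plan says.** Under Specific Aim 2 the clinic is the unit of randomisation: "Thus, there will be two sets of two matched clinics that will then be randomized", one of each pair to team communication training (TCT) and one to the comparison strategy. There are on average 10 clinicians per clinic.

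The Power analysis section uses the program RMASS and lists five assumptions:

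- "An alpha level of .05"
- "a conservative effect size of *d* = .61"
- "standard deviations at each time-point that were increasing in magnitude" ("baseline: SD = 1.00 with SDs increasing by .5 at each subsequent time-point")
- 15% overall attrition
- a lag-1 autoregressive structure, "using an autocorrelation value of .70"

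From these and 20 clinicians per arm it concludes that "we will have 80% power to detect the predicted effect on outcomes".

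The Analytic plan tests a Group x Time interaction over baseline, 3 and 6 months, with clinic as a fixed covariate. It adds: "If a statistically significant (*p* < .05) interaction term is evident, simple slopes analyses will be conducted".

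**The concern.** There are two separate problems.

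**Clustering.** The article prints its full list of power inputs, and none of them describes clinics. TCT is delivered to whole teams, so clinicians in one clinic may change together. The error that matters for a Group x Time test is then how much clinic trajectories vary, and only four clinics are available to show it. A fixed clinic effect removes stable differences between clinics. It does not remove clinic-by-time variation.

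**Reproducibility.** The effect size is given without the SD it refers to and without its shape over time. With SDs that double from baseline to 6 months, these choices move the answer a great deal, and most of them do not give 80%.

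The article says that the results will serve as preliminary data for a later definitive test. A power figure that the design does not have would misstate how precise those data are.

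**Working it through.** **Inputs from the article.** SDs 1.0, 1.5, 2.0; AR(1) correlation 0.70; 15% overall attrition; alpha .05; d = 0.61; 20 per arm; 10 per clinic; 2 clinics per arm.

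**Assumed, because the article does not say.** Two-sided test; retention 1, 0.925, 0.85, so per arm 1.5 leave after baseline, 1.5 after month 3 and 17 complete; ICC for change .01 to .10.

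**Step 1: try to reproduce 80%, ignoring clinics.** With covariance V(s,t) = SD(s) x SD(t) x 0.70^|s-t|, the variances are 1, 2.25, 4 and the covariances 1.05, 0.98, 2.10. Each arm has an intercept and slope, X = [1, t] with t = 0, 1, 2. The information per arm is I = sum over dropout patterns of n_k X_k' V_k^-1 X_k. The standard error of the slope difference is sqrt(2 x [I^-1]_22) = 0.2795 per 3-month interval. Power = Phi(slope difference / 0.2795 - 1.96).

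| Effect (zero at baseline) | Difference at 3, 6 months | Fitted slope difference | Ratio to SE | Power |
|---|---|---|---|---|
| Linear, d in baseline SD | 0.305, 0.61 | 0.305 | 1.09 | 19% |
| Linear, d in pooled SD | 0.474, 0.948 | 0.474 | 1.70 | 40% |
| Linear, d in 6-month SD | 0.61, 1.22 | 0.61 | 2.18 | 59% |
| Step, d in each visit's own SD | 0.915, 1.22 | 0.703 | 2.52 | 71% |
| Step, full 6-month difference by month 3 | 1.22, 1.22 | 0.796 | 2.85 | 81% |

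The pooled SD is sqrt((1 + 2.25 + 4)/3) = 1.55. In the last row the 3-month difference is 1.22/1.5 = 0.81 of that visit's SD, which is larger than the stated 0.61. The fourth row reaches 81% if the test is one-sided.

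**Step 2: grant the 80% and add clinics.** Two-sided 80% power corresponds to a ratio of 1.96 + 0.84 = 2.80. Divide by sqrt(DE), with DE = 1 + (10 - 1) x ICC, where ICC refers to change over time. Then use either the normal critical value 1.96 or a noncentral t on 4 - 2 = 2 df (critical value 4.30).

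| ICC | DE | Ratio | Power, normal | Power, 2 df |
|---|---|---|---|---|
| 0 | 1.00 | 2.80 | 80% | 35% |
| .01 | 1.09 | 2.68 | 77% | 33% |
| .05 | 1.45 | 2.33 | 64% | 27% |
| .10 | 1.90 | 2.03 | 53% | 22% |

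**Step 3: combine the two.** Applying the 2-df calculation to the five shapes in Step 1 over ICC 0 to .10 gives about 7% (linear, baseline SD, ICC .10) to 36% (full step, ICC 0).

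**Step 4: expected precision.** The 6-month difference under a linear slope has SE 2 x 0.2795 = 0.559. The 95% half-width on 2 df, in 6-month SD units, is 4.30 x 0.559 x sqrt(DE) / 2. This is about 1.3, 1.4 and 1.7 at ICC .01, .05 and .10.

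**The case against.** The strongest objection is that the article does not give the effect pattern entered into RMASS, and such a detail may sit in the full protocol. Initial training falls in the first three weeks (Table 1), so an early step is plausible, and one step pattern does pass 80% two-sided without any baseline gap. This stands. A reader might infer that power cannot exceed 59%, that only a gap already present at baseline reaches 80%, or that the real power is 20% to 60%. The documents support none of these. The 59% ceiling holds for linear divergence only, and a range computed without clinics is not the power of a clustered design. Sample sizes of 33 to 39 per arm would give 80% for linear divergence to 0.61 of the 6-month SD. That might suggest the total of 40 was entered as the per-arm number, but nothing in the text shows it.

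It is also fair that the article gives no ICC, that the fixed clinic effect removes stable clinic differences, and that a 2-df test is not what the article plans. The Analytic plan mentions random intercepts and slopes without naming their level, so the analysis itself may allow clinic-specific slopes. None of this rescues the 80%, because the power calculation contains no such variance. If the test leaves out clinic-by-time variation, power is kept only at the price of the error rate: the nominal 5% becomes about 10% at ICC .05 and 16% at ICC .10.

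Finally, this is a pilot of preliminary effects, and the article does not say that a null result would count against TCT. That lowers the consequence but does not make the printed figure correct. The word conservative for d rests on a comparison with a larger published effect, and the power argument gives no ground to delete it.

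**Conclusion.** The point holds in two parts.

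- **Clustering.** This part is firm. The stated power is that of an individually randomised trial, while the design randomises two clinics per arm. Granting 80% at the individual level, power is about 77%, 64% or 53% at ICC .01, .05 or .10 with a normal critical value, and about 33%, 27% or 22% on 2 df. The ICC values are assumptions and refer to change over time. The 2-df figures assume inference at clinic level. On 2 df, power is only 35% even at ICC 0.
- **Printed inputs.** This part is conditional. Ignoring clinics, 80% does not follow under linear divergence (19% to 59%) or an own-SD step (71%), two-sided. About 81% needs the full 6-month difference by month 3. The figure therefore cannot be verified as printed; it has not been shown to be impossible.

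Across all these shapes, with 2 df and ICC 0 to .10, power is about 7% to 36%. The paragraph is wrong as written and should be corrected, but for a pilot the consequence is moderate.

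**What to change.** Rewrite the Power analysis paragraph:

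1. Remove the 80% claim.
2. State the effect's shape over time, the SD to which d refers, and whether the test is one- or two-sided.
3. Give power for the Group x Time contrast with four clusters, cluster-level df and a range of ICC for change (for example .01 to .10, marked as assumed).
4. Present the pilot as estimating the effect, with its expected 95% confidence-interval half-width. On the linear reading and 2 df this is about 1.3 to 1.7 of the 6-month SD.

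No clinics or clinicians need be added and no procedure changes. The only cost is a less favourable power figure.

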#### Dissemination plan

Data will be shared with ClinicalTrials.gov. The research team will also share information with key Rady Children’s Hospital Network partners to help develop the universal depression screening protocol and bring team communication practices to the providers that can benefit from this research. Findings will also be compiled and submitted to peer-reviewed scientific journals for publication. All publications will subsequently be shared with the National Center for Biotechnology Information, PubMed, and the US NIH National Library of Medicine.

## Discussion

Although several healthcare systems have initiated robust depression screening protocols in response to rising depression rates in the pediatric population [5], there is a gap between screening and successful service linkage. Inconsistent communication between providers, particularly across different specialties and service areas, is a key hindrance to an efficient, effective depression treatment cascade. By leveraging team effectiveness research to develop an enhanced TCT strategy, this study can potentially help improve existing depression screening protocols, thereby increasing the frequency of successful mental health service linkage.

Multiple considerations have been made to optimize study operations, but the research team acknowledges certain barriers or limitations that could interfere with a successful workflow. Some organizations and clinicians prefer virtual training that solves issues of travel, time away from clinics, and financial burden. For this reason, TCT will be positioned to be delivered either remotely or in-person.

However, as with any virtual communication, there is always a risk of technology issues that will affect recording focus groups and/or delivering the intervention during Aim 2. These are critical considerations for scalability of strategies such as TCT. In addition, not all staff members may have the adequate time, understanding, or resources to benefit from synchronous virtual training. To mitigate this, medical clinic leaders (physicians and staff) will be engaged during Aim 1 to build buy-in for the TCT activities and to best coordinate research activities within or around clinical operations. The team will also explore approaches such as asynchronous learning that combine recorded and interactive trainings with applied team participation in exercises to consolidate learning and provide teams with experience and practice. Additionally, the research team acknowledges that asking staff members questions during focus groups or qualitative interviews about their experiences with depression screening may give rise to some uncomfortable feelings or reactions. To mitigate this issue, researchers will adhere to Institutional Review Board (IRB) guidelines by providing all participants with an information sheet that reminds them that study participation is voluntary, emphasizing that they can refuse to answer a question or cease participation at any time.

The implementation strategy refined for the depression screening context (Aim 1) and data collected on its effectiveness (Aim 2) and mechanisms (Aim 3) will serve as essential preliminary data for a subsequent definitive test of the TCT implementation strategy. TCT is likely to lead to improved, efficient, and effective decision-making to increase the frequency of depression screening and timely response vis-à-vis appropriate service linkage. We will also identify and leverage team communication language data sources (e.g., focus group transcripts; recordings of team meetings; team meeting notes and written communication) to submit to the IN STEP Methods core for aggregation across IN STEP Center projects. Eventually, measures developed in this process could be used to further develop and guide team training and development activities.

The refined TCT model from this study is expected to result in a better understanding and examples of how to optimize team communication activities and patterns for efficiency and effectiveness in the screening to treatment cascade. This should result in better patient engagement and outcomes. To accomplish and test assumptions, data and results will be used to refine the TCT model and finalize the intervention for a Hybrid Type 3 application focused on scale-up and sustainment of TCT across pediatric health systems implementing depression screening protocols.

## Data Availability

N/A.

## Abbreviations

EHR: Electronic Health Record
IN STEP: Implementation Science and Team Effectiveness in Practice
NLP: Natural Language Processing
PHQ: Patient Health Questionnaire
TCT: Team Communication Training
